## Introduction

Menopause marks a crucial milestone in a woman's life and signals the end of the reproductive life cycle, usually occurring between the ages of 45 and 55 years. The cessation of oestrogen production has a direct effect on various organs in the body and women commonly experience wide-ranging menopausal symptoms, including sleep disturbance, bone loss, brain fog, weight gain, anxiety, depression and fatigue. Hot flushes (or vasomotor symptoms), the major pathophysiological symptom of the menopause, are experienced by ∼80% of women for up to several years (1) and can have a profoundly negative impact on quality of life (2, 3). A hot flush is an extreme thermoregulatory event, characterised by a sudden and intense feeling of heat, skin flushing/reddening and profuse sweating that can be triggered by environmental factors, such as heat stress, alcohol, caffeine and emotional stress, but often hot flushes occur spontaneously. The severity of hot flushes is associated with vascular dysfunction and increased cardiovascular disease risk through changes in cardiometabolic function (3, 4).

Hormone replacement therapy (HRT) can alleviate hot flushes, but is not suitable for all individuals, such as those with a medical history of hormone-receptive cancer, and HRT can also experience poor uptake due to historic links with breast cancer and an increased risk of cardiovascular disease (5). Fezolinetant, a non-hormonal neurokinin-3-receptor (NK_3_R) antagonist that dampens central thermoregulatory mechanisms associated with moderate to severe vasomotor symptoms, has recently been licensed for private prescription in the UK, but is not yet widely available. Few alternative treatments are available and consequently, many females suffer the debilitating symptoms of hot flushes due to a lack of therapies, and, ultimately, an incomplete understanding of the physiological mechanisms underpinning hot flushes.

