### Eligibility criteria

Potential participants will exclude themselves based upon the detailed inclusion/exclusion criteria (Table 1) provided on recruitment material and the PIS. These criteria reflect the practical requirements of the study, to ensure that research findings are valid and to ensure the safety of participants. Participants will be consented and screened, consisting of medical history and details of current medications. Postmenopausal participants will complete a 7-day hot flush diary (25). Members of the research team will review completed screening information to confirm eligibility to participate.

**Table 1 T1:** Detailed inclusion and exclusion criteria.

Detailed inclusion criteria		
Postmenopausal + Hot Flush	Postmenopausal	Premenopausal
• Female • Aged 45–65 years • Amenorrhoeic for >6 months • >4 Hot flushes per day • Not on medication or treatments to alleviate hot flushes e.g., HRT	• Female • Aged 45–65 years • Amenorrhoeic for >6 months	• Female • Aged 18–40 years • Eumenorrheic
AND		
• Healthy • Non-smoker/non-vaper • BMI 18–30 kg/m^2^ • No history of cardiovascular or respiratory disease • No history of metabolic diseases e.g., type II diabetes • Drink <14 units of alcohol per week • Participant is willing and able to give informed consent for participation in the study.		
Detailed exclusion criteria		
• Cannot readily read and understand English • Aged <18 years, 41–44 years or >65 years • Male • Current smoker/vaper • BMI <18 or >30 kg/m^2^ • Medical history of cardiovascular/respiratory disease • Medical history of metabolic disease e.g., type II diabetes • Drink >15 units of alcohol per week • Vaccination (<1 week) due to induced systemic inflammatory reaction • Local forearm infection • Allergy to local anaesthetic/Marcaine/amide-group anaesthetics • Currently pregnant, or planning on becoming pregnant • <6 Months postpartum or stopped breast feeding <1 month before recruitment • On medication or treatments to alleviate hot flushes or have taken such medication/treatments within the previous 6 months e.g., HRT		

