#### Secondary outcomes

Anthropometric data (e.g., height and weight), age and ethnicity will be collected. Resting blood pressure will be recorded at baseline and at intervals throughout the first visit. A single venous blood sample will be collected at the first visit to measure oestradiol and circulating pro-inflammatory markers.

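### Table 1 establishes postmenopausal status only by age 45–65 and more than 6 months' amenorrhoea, so women who still produce oestrogen can be analysed as postmenopausal

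*Protocol article*

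**What the plan says.** Table 1 (Eligibility criteria) is presented as the detailed list of criteria. Beyond female sex and an age limit of 45 to 65, the postmenopausal hot-flush group is defined by "Amenorrhoeic for >6 months • >4 Hot flushes per day", with the further condition that flushes are not being treated. The second postmenopausal group has the same age and amenorrhoea lines without the flush line. General health criteria apply to everyone.

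Three exclusions bear on why a woman might have no periods or altered hormones. Two concern reproduction: a current or intended pregnancy, and childbirth in the last 6 months or lactation that ended within the last month. The third concerns treatment: "On medication or treatments to alleviate hot flushes or have taken such medication/treatments within the previous 6 months e.g., HRT".

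Screening is described as follows: "Participants will be consented and screened, consisting of medical history and details of current medications". In addition, the postmenopausal groups keep a flush diary for 7 days. No hormone test is part of screening.

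Oestradiol appears under Secondary outcomes: "A single venous blood sample will be collected at the first visit to measure oestradiol and circulating pro-inflammatory markers". Under Blood sample, the aliquots are frozen and assayed later by ELISA.

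The Introduction gives the biological premise: "The cessation of oestrogen production has a direct effect on various organs in the body". It places menopause usually between 45 and 55 years. The Abstract and Introduction attribute the expected changes in skin vessels and sweat glands to oestrogen deficiency or withdrawal.

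**The concern.** This is an observational comparison, so group membership is the exposure. The exposure of interest is loss of ovarian oestrogen, but the criterion records only the absence of bleeding. The two can come apart. A woman of 48 with a hormonal coil, or with her uterus removed and her ovaries working, has no periods and may have normal oestrogen. A woman of similar age with 7 months of amenorrhoea may still be in the transition.

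If such women are counted as postmenopausal, the pre- versus postmenopausal difference is pulled towards zero in groups of 12, and a null result could not be read as absence of an oestrogen effect. The plan collects a measurement that could expose the problem, but no section says it will be used for that.

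**Working it through.** **1. Does Table 1 let such women in?** Each case is set against the listed criteria, assuming that she is female, healthy, aged 45–65 and meets the flush line where it applies.

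| Cause of more than 6 months' amenorrhoea | Removed by a stated rule? |
|---|---|
| Pregnancy | Yes |
| Less than 6 months postpartum, or breast feeding stopped less than 1 month before recruitment | Yes |
| Flush treatment such as HRT, current or within 6 months | Excluded as a treatment |
| Hormonal coil or progestogen contraception | No: the exclusion is limited by purpose, to alleviating flushes |
| Hysterectomy or endometrial ablation, ovaries working | No |
| Menopausal transition | No: only the 6-month limit and the age range apply |
| Removal of both ovaries | No, but this does produce oestrogen deficiency, so it is not a misclassification |

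The age range limits the problem without removing it. The protocol's usual age at menopause, 45–55, is the lower half of its 45–65 range, so amenorrhoea in that half need not mark established postmenopause.

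**2. Is there a later check?** Eligibility is confirmed from screening information. Oestradiol is drawn at visit 1, after that decision, and assayed from frozen samples. The analysis text under Visit 1 names fixed effects of dose and/or group, and that under Visit 2 names a one-way ANOVA. Neither mentions oestradiol.

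**3. Size.** The plan gives no figure for the share m of postmenopausal women who are not oestrogen-deficient, and none for the pre- versus postmenopausal effect. What follows is an illustration only. It assumes that:

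- misclassified women respond like premenopausal women;
- the true pre- versus postmenopausal difference is 1 SD (the plan ties its effect size of 1 to the flush contrast, so this is borrowed);
- 12 women are compared with 12 by a two-sided 5% t-test (alpha and sidedness are not stated).

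The plan's own figure comes first. At a standardised difference of 1 and 12 per group, this test has power 0.65, not the stated 0.9, which would need 22.02, so 23, per group. That mismatch is a separate matter and the present point does not depend on it.

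For misclassified share m:

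- expected difference = 1 − m
- variance in the mixed group = 1 + m(1 − m)
- standardised difference = (1 − m) / √{[1 + 1 + m(1 − m)] / 2}

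For m = 0.2 this is 0.8 / √[(1 + 1.16)/2] = 0.8 / 1.039 = 0.77.

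| m | Expected difference (SD) | Standardised difference | Power, 12 v 12 |
|---|---|---|---|
| 0 | 1.0 | 1.00 | 0.65 |
| 0.1 | 0.9 | 0.88 | 0.54 |
| 0.2 | 0.8 | 0.77 | 0.44 |
| 0.3 | 0.7 | 0.67 | 0.35 |

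The table shows how sensitive groups of this size are. It does not estimate the loss in this study.

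**The case against.** The best defence has three parts.

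First, an article condenses a full protocol, and medical history and medications are reviewed before entry, so the team may turn such women away. It is true that the information is collected. But the table is offered as the detailed criteria, and potential participants are told to exclude themselves by it. It deals explicitly with some causes of amenorrhoea and stays silent on these. No stated rule tells the team to exclude them.

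Second, use of oestradiol in a sensitivity analysis is commonly left to an analysis plan, which is not at hand. This stands in part: the documents do not show that oestradiol will be used only descriptively, just that no stated use checks group. The point therefore rests mainly on the eligibility rule.

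Third, a single oestradiol sample is an imperfect check. Study limitations concedes that one-time sampling misses hormonal fluctuations, and a woman in transition can have a low value on the day. This stands and limits what the check can deliver.

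Some stronger readings are tempting but not supported:

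- That amenorrhoea from any cause qualifies. Pregnancy, recent childbirth and recent breast feeding are excluded.
- That hormonal contraception is admitted in all groups. Premenopausal women must be eumenorrheic and attend on cycle days 1–5, which presumes regular cycles. The gap is clear only in the postmenopausal groups.
- That the plan breaches a 12-month definition. The documents contain no such standard.

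**Conclusion.** The point holds for the definition of the postmenopausal groups. A woman whose amenorrhoea comes from hormonal contraception, or from uterine surgery with working ovaries, meets every listed criterion, and so may a woman in transition. The consequence is dilution of the pre- versus postmenopausal contrast. Its size cannot be estimated, because the documents give neither the share of such women nor how they would respond.

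A reader might also infer that the flush versus no-flush contrast is biased because women in transition gather in the flush group. Nothing in the documents supports that. Nor do the illustrative power figures carry over to that contrast: they assume that misclassified women show none of the effect, and there is no basis for supposing that a woman in transition with more than 4 flushes a day responds like a woman without flushes.

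The defect deserves correction. It does not invalidate the study.

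**What to change.** **Eligibility, postmenopausal groups only.** Add that the amenorrhoea must not be explained by hormonal contraception, or by hysterectomy or ablation with ovaries kept. Apply this from the medical history and medication list already taken at screening. Removal of both ovaries need not be excluded on this ground. The cost is slightly slower recruitment. Recruitment was planned for 12 months from October 2024, so this change may reach few or no new participants.

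**Sensitivity analysis, all women enrolled, including those already recruited.** Before unblinding, pre-specify a repeat of the primary comparisons limited to postmenopausal women whose visit 1 oestradiol lies in the assay's postmenopausal range, and write down that range in advance. No new test is needed. The costs are a smaller set drawn from groups of 12, hence wider intervals, and the chance that one sample leaves some women in transition in the set.

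Time since last period should not be added as a covariate to the three-group model. In premenopausal women it is near zero by design (cycle days 1–5), so it is confounded with group. It also does not date menopause in women whose amenorrhoea is contraceptive or surgical, and the documents do not say it is recorded.

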The skin undergoes many morphological changes with advancing age (e.g., reduced collagen content and elasticity) which is accelerated with oestrogen withdrawal, resulting in reductions in collagen content, elasticity, water content and thickness (20). It is unknown if hypo-oestrogenism affects key vascular, sudomotor and/or neural structures in the skin, which also play a role in hot flushes. The number of sweat glands is generally constant across the lifespan in healthy individuals, but they are sensitive to repeated or a lack of stimuli. More specifically, the size of sweat glands and the number and density of the sympathetic nerve endings surrounding sweat glands can reduce as a result of decreased use (21). Similarly, the number of skin blood vessels can decrease with aging (22, 23), as they are also sensitive to repeated (or lack of) stimuli (24) leading to a reduction in both number and size when there are no recurring elevations in blood flow.

It is currently unknown whether the structure of skin blood vessels and/or sweat glands is affected by menopause or if they contribute to the occurrence of hot flushes. Furthermore, it remains uncertain whether there is a relationship between the function of skin blood vessels and/or sweat glands and the occurrence of hot flushes.

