### Sample size calculation

Based on previously reported differences in post-ganglionic skin blood flow responses between postmenopausal women with and without hot flushes (17–19), a power (1-β) of 0.9 and an effect size of 1, 24 postmenopausal women (12 who experience hot flushes and 12 who do not) and 12 premenopausal women will be recruited for this study.

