## Discussion

The aim of this novel study is to examine both function and structure of skin blood vessels and sweat glands in pre- and postmenopausal women, who do and do not experience hot flushes. Findings from this work will reveal whether menopause is associated with altered function of skin blood vessels and sweat glands, such as an overt sensitivity to vasoactive substances that contributes to hot flushes. Furthermore, the study will examine whether menopause affects the structure of skin blood vessels and/or sweat glands, and whether a relationship exists between the function and/or structure of skin blood vessels and/or sweat glands, and the occurrence of hot flushes. Observation of any such changes in function and/or structure would increase our understanding of the causes and side effects of hot flushes, which would have important implications for patients and clinicians by helping in the design of effective treatments. Such therapies may include interventions that can manipulate the activity of the skin blood vessels and/or sweat glands via pharmacological and non-pharmacological methods.

Hot flushes, experienced by ∼80% of postmenopausal women, have a profoundly debilitating effect on daily activities and quality of life (1). Whilst menopausal hot flushes are widely recognised as being extreme thermoregulatory events with episodes typically lasting for several minutes and ranging from a few times per week up to several episodes per hour, their underpinning mechanisms are not well understood which has consequently limited scientific advances in hot flush therapies. Previous work has suggested mechanisms related to a narrowed null zone in the core temperature range of menopausal women reducing the temperature threshold for the onset of sweating, such that sweating will be activated and a hot flush triggered when an increase in core temperature surpasses the lowered threshold (34). However, this hypothesis is disputed as a further study observed that 49% of women did not experience a subtle increase in core temperature prior to a hot flush (35).

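### The pre/post comparison combines ageing with menopause because the age ranges do not overlap, yet the Discussion reads it as menopause alone

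*Protocol article*

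**What the plan says.** **Ages (Eligibility criteria, Table 1).** The premenopausal group is "Female • Aged 18–40 years • Eumenorrheic". The postmenopausal group without hot flushes is "Female • Aged 45–65 years • Amenorrhoeic for >6 months", and the group with hot flushes has the same age limits. The exclusion list closes the space between them: "Aged <18 years, 41–44 years or >65 years".

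**Ageing (Introduction).** The protocol says that skin morphology changes as people age, that oestrogen withdrawal speeds this up, and that "the number of skin blood vessels can decrease with aging".

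**Analysis (Visit 1 and Visit 2).** Function is compared between the pre- and postmenopausal cohorts, with an exploratory mixed model in dose and/or group. Structure is compared by one-way ANOVA, with pre versus post as the example. Age is collected (Secondary outcomes).

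**Conclusions (Discussion).** On function: "Findings from this work will reveal whether menopause is associated with altered function of skin blood vessels and sweat glands". On structure, the study is to examine whether menopause has an effect.

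**Study limitations.** The section says that an observational design supports no causal conclusion. It then lists sample size, single region, diary reporting, single biopsy site and single-time sampling. Age is not mentioned.

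**Sizing (Sample size calculation).** The study was sized on "differences in post-ganglionic skin blood flow responses between postmenopausal women with and without hot flushes", giving "24 postmenopausal women (12 who experience hot flushes and 12 who do not) and 12 premenopausal women will be recruited".

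**The concern.** If every premenopausal woman is at most 40 and every postmenopausal woman at least 45, a difference between them in vessel number, vessel size or gland size could come from ageing, from menopause or from both. The protocol names ageing as a cause of change in skin structure and then does not carry it into the interpretation. A reader of the results would take a pre/post difference as evidence about menopause or oestrogen loss when the design cannot show that. The general remark about causality does not warn of this: what is inseparable from age is the association itself, before any question of cause.

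**Working it through.** **1. Can the two be separated?** Write the expected outcome as f(age) + τ × status. Under Table 1, status is 0 whenever age is 40 or below and 1 whenever age is 45 or above. No eligible age has both states. Any value of τ can therefore be offset by a change in f across the empty interval, and τ is not identified unless a shape for f is imposed. This step needs no numbers from outside the protocol.

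**2. What if a linear age term is imposed?** Assume ages uniform within each range.
- Midpoints: (18 + 40)/2 = 29 and (45 + 65)/2 = 55, a gap of 26 years.
- Within-group variances: 22²/12 = 40.3 and 20²/12 = 33.3.
- For 12 versus 24, the between-group sum of squares is (12 × 24/36) × 26² = 5408. The within-group sum is 11 × 40.3 + 23 × 33.3 ≈ 1210.
- Variance inflation 1/(1 − r²) = (5408 + 1210)/1210 ≈ 5.5, so r ≈ 0.90.
- For 12 versus 12: 6 × 26² = 4056, within ≈ 810, inflation ≈ 6.0, r ≈ 0.91.

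Power at a true difference of 1 SD (two-sided 0.05, t test):

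| Groups | No age term | Linear age term |
|---|---|---|
| 12 vs 24 | 0.78 | about 0.22 |
| 12 vs 12 | 0.65 | about 0.16 |

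For 12 versus 24 the adjusted standard error is √[(1/12 + 1/24) × 5.46] ≈ 0.83 SD, against 0.35 SD without the age term. Even then the estimate depends on extrapolating a straight line across ages that nobody in the study has.

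The 0.65 for 12 versus 12 is below the stated "a power (1-β) of 0.9 and an effect size of 1". That is a separate question about the sample size, and nothing here depends on it.

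**3. How large could an age-only difference be?** The document gives no ageing slope and no expected ages. Assume slopes of 0.01–0.04 SD per year, groups at their midpoints and no menopause effect. Then d = 26 × slope. The chance of a significant pre/post result follows from the noncentral t distribution, two-sided 0.05, noncentrality d/√(1/n₁ + 1/n₂):

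| Slope (SD/year) | d | 12 vs 24 | 12 vs 12 |
|---|---|---|---|
| 0.01 | 0.26 | 11% | 9% |
| 0.02 | 0.52 | 30% | 23% |
| 0.03 | 0.78 | 57% | 45% |
| 0.04 | 1.04 | 82% | 68% |

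A Bonferroni adjustment for three group comparisons (0.05/3), 12 versus 12, lowers the last column to about 4%–50%. A slope of 1/26 ≈ 0.04 SD per year would by itself produce the protocol's planning effect of 1 SD.

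**4. Which comparison is affected?** Only pre versus post. Both hot-flush groups share the 45–65 range, so ages overlap there and an age term can be estimated.

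**The case against.** The other side has a fair case, and much of it limits the point.

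- *The protocol does not claim causation.* A reader might infer that it promises to show that menopause alters function and structure. It does not: for function it speaks of association, the verb of effect appears only for structure and only as something to be examined, and the limitations disclaim causality. What remains is that the disclaimer never names age.
- *The main comparison is sound on this point.* A reader might infer that the whole study is undermined. The comparison used for sizing is within the postmenopausal women, and the age gap does not reach it.
- *The stated age evidence is narrow.* The Introduction gives an age effect on skin morphology and vessel number. The structural primary outcome is vessel and gland size, and gland number is said to be broadly constant over life. The document states no age effect on blood-flow or sweating responsiveness. Bias in responsiveness is possible, but the document does not establish it.
- *Covariates belong in an analysis plan.* For the hot-flush comparison this is right. The absence of a stated age term there is no error, and no imbalance is built in. For pre versus post it does not help, because eligibility rules out an analytic remedy.
- *The rates are assumed.* They are, and their range runs from slight to severe.
- *Age and natural menopause always go together to some degree.* The protocol puts menopause usually at 45–55, so a cross-sectional study will struggle. That is a reason to say so in the limitations.

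**Conclusion.** The point holds in a limited form. The lack of overlap is a fact of Table 1 and needs no assumption: the pre/post difference is a combined effect of age and menopause, and no analysis of these groups can divide it. The Discussion words it as a finding about menopause, and the limitations do not warn the reader about age.

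The percentages (11%–82% for 12 versus 24, 9%–68% for 12 versus 12, unadjusted) are illustrations. They rest on assumed slopes and midpoint ages and should not be read as estimates of the study's false-positive rate. The power figures with an age term rest on uniform ages and a linear effect.

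This should be fixed because it changes what the study can conclude from one of its named comparisons. It does not call for redesign, and it leaves the hot-flush comparison intact.

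**What to change.** 1. **Reword the Discussion and add to Study limitations.** State that the premenopausal and postmenopausal groups have no ages in common, that any difference between them is a combined age-and-menopause difference, and that it cannot be attributed to menopause or oestrogen loss. Use the same wording for function and structure. This costs a few sentences and can be done at any stage.
2. **Include age as a covariate in the comparison of postmenopausal women with and without hot flushes.** Ages overlap there and age is already collected. The cost is one degree of freedom.

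Two other changes are not recommended. Matching the hot-flush groups on age may come too late, since recruitment was planned for October 2024 to October 2025. Steering premenopausal recruitment to ages 35–40 has the same timing problem, and it still leaves no overlap and a midpoint gap of 55 − 37.5 = 17.5 years. Under the same slopes that gives 8%–49% for 12 versus 24.
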